## Abstract

**Background:**

Current Canadian evidence illustrating the health benefits and cost-effectiveness of caregiver-friendly workplace policies is needed if Canadian employers are to adopt and integrate caregiver-friendly workplace policies into their employment practices. The goal of this three-year, three study research project is to provide such evidence for the auto manufacturing and educational services sectors. The research questions being addressed are: What are the impacts for employers (economic) and workers (health) of caregiver-friendly workplace policy intervention(s) for full-time caregiver-employees? What are the impacts for employers, workers and society of the caregiver-friendly workplace policy intervention(s) in each participating workplace? What contextual factors impact the successful implementation of caregiver-friendly workplace policy intervention(s)?

**Methods:**

Using a pre-post-test comparative case study design, Study A will determine the effectiveness of newly implemented caregiver-friendly workplace policy intervention(s) across two workplaces to determine impacts on caregiver-employee health. A quasi-experimental pre-post design will allow the caregiver-friendly workplace policy intervention(s) to be tested with respect to potential impacts on health, and specifically on caregiver employee mental, psychosocial, and physical health. Framed within a comparative case study design, Study B will utilize cost-benefit and cost-effectiveness analysis approaches to evaluate the economic impacts of the caregiver-friendly workplace policy intervention(s) for each of the two participating workplaces. Framed within a comparative case study design, Study C will undertake an implementation analysis of the caregiver-friendly workplace policy intervention(s) in each participating workplace in order to determine: the degree of support for the intervention(s) (reflected in the workplace culture); how sex and gender are implicated; co-workers’ responses to the chosen intervention(s), and; other nuances at play. It is hypothesized that the benefits of the caregiver-friendly workplace policy intervention(s) will include improvements in caregiver-employees’ mental, psychosocial and physical health, as well as evidence of cost-benefit and cost-effectiveness for the employer.

**Discussion:**

The expected project results will provide the research evidence for extensive knowledge translation work, to be carried out in collaboration with our knowledge transition partners, to the employer/human resources and occupational health/safety target populations.

**Trial registration:**

ISRCTN16187974 Registered August 25, 2016.

**Electronic supplementary material:**

The online version of this article (10.1186/s12889-017-4722-9) contains supplementary material, which is available to authorized users.

## Background

In the past century, the most significant demographic transition in Canada that has revolutionized the labour force is the increase in female participation. This has been beneficial to the Canadian economy, but regrettably has had an impact on stress-related illness, such as cardiovascular disease; once a predominantly male pathology, it now accounts for at least 41% of all deaths of Canadian women in comparison to 37% for men [1]. Higher levels of stress for working women due to role strain negatively impacts their health and well-being [1]. Like paid labour, unpaid labour in the form of family care is also gendered, largely due to persistent gendered expectations that women assume domestic duties, compounded with gendered beliefs that women are inherently better at and more suited to caregiving than men. Moreover, women caregivers spend more hours per week involved in care tasks and typically are more likely to be engaged in care activities that must be done in person on a regular basis (e.g., personal care, food preparation) [2]. The majority of caregiver-employees (CEs) are women, and their participation in the workforce provides both social and financial support to their unpaid caregiving role, although the latter is linked with reduced mental and physical health [3]. Similarly, fulfilling the challenges of cultural and familial obligations while engaging in paid labour can lead to psychological stress, less time for self-care, and role conflict [4], as is seen in many cultures where women are expected to sacrifice their own needs for the needs of their husband, children, elderly parents, and in-laws.

The CE, faced with managing simultaneous paid work and unpaid care responsibilities, often encounters role strain (having to balance multiple work-family roles and responsibilities), forcing them to sacrifice one of their two roles and/or face negative health outcomes. These negative health outcomes which result from role strain can have a great impact on CEs’ health. CEs are defined as family members or friends who are providing care to an elder care recipient (often at home), while also engaging in paid employment. This new category of worker, created through numerous demographic changes and community health care provision realties of the twenty-first century, has brought attention to the need for support for family members and friends providing unpaid care. One strategy is through caregiver-friendly workplace policies (CFWPs). CFWPs, often termed family-friendly workplace policies, are defined as “deliberate organizational changes – in policies, practices, or the target culture – to reduce work-family conflict and/or support employees’ lives outside of work” [5]. Current Canadian evidence illustrating the health benefits and cost-effectiveness of CFWPs is needed if Canadian employers are to adopt and integrate CFWPs into their employment practices; otherwise they will continue to be reluctant to introduce CFWPs.

Since the 1990s, there has been an increased recognition of the need for financial and job security for caregivers [6–9], as well as relief from the role strain of what has been termed ‘the double day’ or the ‘second shift’. Workplace overload can lead to spill-over effects at home, and home stress due to caregiving can lead to negative effects at work, particularly for women who do not disengage as much after work compared to men [10]. With caregivers in Canada providing an estimated $26 billion of unpaid work, the Canadian health care system relies on informal unpaid care to support an aging population [11]. To address the problem of financial and job security, the Canadian government has implemented a number of programs for caregivers, such as the Compassionate Care Benefit (CCB) and caregiver and other tax credits. However, despite these attempts to provide informal unpaid caregivers with much-needed financial support and respite, policy-makers are coming to the realization that this is not enough. Rather, support needs to come from employers as well [7, 12–15]. For employers, there are several advantages to creating CFWPs. The potential costs of these policies can be offset by increased employee retention and less employee turnover, reduced absenteeism and presenteeism (i.e., engagement in work), and a positive company reputation, which can be beneficial both for business and for employee recruitment [2, 16–20]. In 2007, Canadian businesses lost over $1.3billion in productivity, as a result of informal unpaid caregivers missing full days of work, missing hours of work, or even quitting or losing their jobs [21]. Thus, from a business perspective, employers have much to gain financially from offering CFWPs, while simultaneously decreasing role strain, negative health outcomes and risk of occupational injury for CEs. This not only improves CEs’ job satisfaction but positively impacts CEs’ overall health [22–31]. Considering that informal unpaid caregivers play a significant, dual economic role in Canadian society, it is imperative to seek strategies that minimize or alleviate inequitable caregiver burden and the potential negative health outcomes which can arise for CEs [32].

Despite their potential benefits, many companies do not currently offer CFWPs [15]. The literature suggests a variety of reasons, including: the lack of initiative on the part of employers; the perceived challenges of implementing CFWPs; or organizational limitations, such as a small staff or a lack of human resources (HR) personnel [17, 33–35]. Studies have shown that employers with a relatively large staff, the presence of an HR department, and women in high-ranking senior positions are more likely to implement CFWPs because they have the knowledge, experience, and resources to do so [17, 31, 33, 34]. Workplaces that have a high use of technology are also more likely to accommodate CEs, as technology often lends greater work flexibility [36]. While different CFWPs have been used to varying degrees in almost every industry, the financial (banking, accounting, insurance) and public sectors currently appear to be the most innovative and advanced [17, 33, 34]. The manufacturing, transportation and construction sectors are the least developed, perhaps owing to the male-dominated workforce of many of these industries. Industries that are typically dominated by men may not view caregiving as an issue that their employees will encounter (given gendered assumptions about caregiving), and thus may not be aware of the value of implementing CFWPs [34].

Within the research literature, a variety of CFWPs have been identified as either being currently in use by selected employers across the globe, or proposed as potentially beneficial policies. From this review of literature, the most commonly identified CFWPs include: flexible work schedules; reduction of hours to part-time, and; unpaid care leaves (at time periods beyond the government-mandated timeframe) [34, 37]. Other CFWPs include: job-sharing; working from home (either part-time or full-time); transfer to a different branch that is closer to home; and the ability to work compressed work weeks [36]. Further, certain employers have also hired external companies or appointed HR staff to provide support services, such as: resource referral; information services; counseling; support groups; workshops; and seminars on caregiving issues [17, 34]. In exemplary cases, employers will offer extensive support in the form of: case management services; subsidized caregiving services; adult day care facilities; emergency short-term care; dependent care; flexible spending accounts; web-based support groups or seminars; and dependent-care car parks [34]. Clearly, such CFWPs require the re-allocation, if not re-investment, of resources by employers, whether HR, monetary, or other. Such CFWP initiatives begin with employers’ willingness to examine the research evidence that points to positive health outcomes for CEs.

Lack of workplace support for CEs can result in: CEs leaving the workforce, missed work days, early retirements, reduced productivity, and avoidable costs to employers. Employers need to step up to the challenge of managing a workforce which is, due to health care restructuring, increasingly expected to provide care to family members, often at home. Recognizing that all workplaces will be affected by these caregiving demands, and given population aging, the changing and dynamic nature of families (i.e. greater proportion of females in the workforce, smaller family sizes, increased mobility), together with the changing nature of caregiving (i.e. growing number of male caregivers, fewer publically-provided community services), it is incumbent upon Canadian workplaces to put in place CFWPs to appropriately accommodate CEs. Doing so is not only ethical but provides many advantages for the workplace, particularly given predicted skilled labour shortages. Uptake of CFWP intervention(s) by workplaces will likely depend on a number of factors such as funding availability, priorities in other domains, and precedence. Invariably, a key piece of information is the resource implications (both costs and consequences) of the chosen intervention(s). Knowledge about the resource implications of intervention(s) alternatives is critical. It provides invaluable information for making choices regarding investments of scarce resources, and is often a key input to the decision of whether to go forward with, expand, or downsize a particular intervention(s).

Given the context of the gendered nature of both paid employment and unpaid family care work, CFWPs exist at the intersection between sex/gender, work and health. As such, this project is framed within gender relations theory. Gender relations theory posits the need to better understand health-related behaviours in the context of interactions within and between women and men across numerous settings, including the personal, interpersonal and institutional levels [38]. As described by Bottorff et al., [38] a gender relations approach recognizes the central role of gender relations in health, including gender dynamics and the interactions thereof, in influencing both health opportunities and constraints. Connell’s gender relations theory is particularly suited to the phenomenon of working-caregiver strain, because it conceptualizes gender relations as being dynamic and performed daily via social interactions and practices [39]. In order to properly understand where and how CFWPs can be implemented, it is necessary to consider how both paid work and unpaid care are impacted by sex/gender. This can help ensure that CFWPs are able to reach the majority of CEs, while also best accommodating CFWPs to meet the needs of a growing number of male CEs. Moreover, CFWPs will likely differ depending on the presence or absence of sex/gender-dominance within a given industry. The results of this research will address a critical information gap, thereby providing evidence to employers about the importance of supporting CEs as a means of improving health, as well as reducing avoidable business costs. Framing two of the studies within gender relations theory will be coupled with an intersectionality approach to analysis [32], allowing for the examination of a number of axes of difference, such as sex/gender, employment status, ethnicity, geography, and income status, to be examined simultaneously.

## Methods

Three objectives will be addressed in three studies, Study A: Pre-Post Test of CFWP Intervention(s); Study B: Economic Evaluation of CFWP Intervention(s); and Study C: Implementation Analysis. These three studies share a number of commonalities, including using a comparative case study approach. The two participating employers represent different sectors of the workforce, making a strong argument for a comparative case study research design for all three studies, and particularly so for Studies A and C. The two participating employers represent the educational and auto manufacturing sectors in Canada. The features of a case study design benefit from complex and context-dependent research, such as the lived experience of CEs participating in the intervention(s). These design features include: comprehensive (longitudinal) and flexible data collection; data and investigator triangulation; comparability; and ability to select purposive examples for maximum diversity (i.e. in composition and variation). Written informed consent will be received for all participants recruited into this study. The qualitative data collected from each of the two of the studies (A and C) will be organized independently and stored via a computerized qualitative data management programme, NVivo10. All audiotaped qualitative data will be transcribed verbatim, imported into NVivo10, and thematically analyzed by the investigative team. The quantitative data collected via Study A and B will be analyzed separately using SPSS.

Each of the three studies will be conducted by a separate graduate student trainee, under the supervision of the Primary Investigator (PI) and, in the case of Study B, a Co-Applicant. Given that the studies will be implemented concurrently, the three graduate student trainees involved will have many opportunities for communication and exchange specific to each of their projects; this will allow them to learn from one another to assure timely success and productivity.

### Study a (objective 1): Pre-post test of CFWP intervention(s)

Using a pre-post test comparative case study design, Study A will determine the effectiveness of newly implemented CFWP intervention(s) across the two identified workplaces to determine impacts on CEs’ health. The intervention(s) will operate like a natural experiment, where a quasi-experimental pre-post design will allow the CFWP intervention(s) to be tested with respect to impact on CEs mental, psychosocial and physical health.

The intervention(s) will be chosen predominantly in consultation with the workplaces involved (i.e. with employers, HR departments, occupational health and safety representatives, and employees, etc.). This process is scheduled to take the first two months of the first year. Here, the research team will bring forward a summative report from an international synthesis of CFWPs, providing each employer partner team with a wide range of CFWPs from which to choose. The bi-weekly meetings, held throughout the initial two-month period of the grant (four meetings in total), will also determine which particular component of the workforce in each of the respective workplaces will be targeted for the research intervention(s), given the gendered nature of caregiving and the knowledge accrued specific to the age range where this is particularly salient (40–65 years).

Defined by the sample size calculation (See Additional file 1) [40], 37 CE participants in each workplace will be recruited into the study. This will provide a total sample of 74 participants across both workplaces. In addition to collecting socio-demographic data on participants, including sex and gender (via the BSRI), non-invasive health measures will be captured in both the pre- and post-implementation stages, including: self-reported health (SF12), self-rated burden (SRB), general self-efficacy (GSE), stress (RSS), mental health (CES-D), and psychosocial health (CRA). If sex and/or gender are not evenly represented in the participant sample, sex- and/or gender-specific CEs will be targeted. Within the 12 month intervention period, the time between the pre- and post-implementation stages will be reflected by the uptake/application of the intervention(s), both quantitatively (i.e. number of CEs using the intervention(s)) and qualitatively (i.e. intensity of use). Given the experience of other such intervention(s) studies, we hypothesize a minimum 25% increase in self-reported health (SF12). Given the size of each of the workplaces, we do not expect to have any difficulties recruiting 37 CEs participants per workplace. Even so, we will recruit as many CE participants as possible as a contingency plan. (see Additional file 1 for a range of sample size possibilities).

The quantitative data collected in Study A will be analyzed by way of descriptive statistics and ordered logit regression. SPSS Statistics software will be used (already purchased and in place at McMaster University). Summary statistics (including a differences between means test and contingency tables) will be produced to test for significant differences (*p* = 0.05) between pre and post-test data points. Tests will also be carried out to assess differences between CEs in each of the two workplaces concerned. A series of ordered logit regressions will be carried out to examine the association between levels of self-reported health – SF12 (the dependent variable) and the collected socio-economic variables (the independent variables). The regression models will assess differences in outcomes between CEs employed in various types of work (i.e. secretarial versus management versus assembly) in each of the two workplaces. The results of this analysis will inform the qualitative portion of the research.

A sub-sample of participants in each workplace will be invited to participate in a qualitative comparative case study (*n* = 20 CE participants; 10 in each workplace) to gather audio-taped, semi-structured in-depth interview data on the experience of having participated in the intervention(s), capturing the effectiveness of the intervention(s) outside of the quantitative variables examined in the pre-post test. Following the post-test data collection point, CE participants will be asked about specific ways in which the intervention(s) have impacted their experience of role strain, caregiver burden and overall health. The interviews will be transcribed verbatim. Guided by an intersectionality approach, this research will address meaningfully the ways in which social categories, such as sex/gender, and employment status intersect to impact CE health.

It is hypothesized that the benefits of the CFWP intervention(s) will include a number of health improvements for CEs, such as a decrease in role strain and improvements in CEs’ mental, psychosocial and physical health.

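### Study A's only regression models SF12 level without a pre/post term or baseline SF12, so it cannot show which job types changed and may pass off standing health gaps as unequal policy benefit

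*Protocol article*

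**What the plan says.** All of this is in the Methods, Study A (objective 1) section of the protocol article.

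- Aim: "a quasi-experimental pre-post design will allow the CFWP intervention(s) to be tested with respect to impact on CEs mental, psychosocial and physical health".
- Hypothesis: "we hypothesize a minimum 25% increase in self-reported health (SF12"). No baseline mean, SD or within-person correlation is given.
- Size: "37 CE participants in each workplace will be recruited into the study"; "This will provide a total sample of 74 participants across both workplaces".
- Timing: "non-invasive health measures will be captured in both the pre- and post-implementation stages", and SF12 is one of these measures.
- Methods: "The quantitative data collected in Study A will be analyzed by way of descriptive statistics and ordered logit regression".

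The section then splits the work. Summary statistics, including a test of the difference between means and contingency tables, compare pre with post at the 0.05 level. The regression is a separate step: "A series of ordered logit regressions will be carried out to examine the association between levels of self-reported health", with its two sides given as "the dependent variable) and the collected socio-economic variables (the independent variables". Its stated use is to compare outcomes between types of work (secretarial, management, assembly) in each workplace. Its results then feed the qualitative part of the study.

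**The concern.** In a pre-post effectiveness study, a comparison of outcomes between job types will naturally be read as showing who gained from the policy. The regression as specified cannot show that. The outcome is SF12 level and the predictors are socio-economic characteristics. Neither the period nor the pre-policy SF12 value is among them. If assembly workers had poorer health than managers before the policy, and both groups changed equally, the model would still report a job-type difference.

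Two things are at stake. Employers could be told that a policy worked better for one kind of worker when the difference was there at the start. The same misreading could also steer the interviews, since the section says that these results inform them. Separately, the output is on the wrong scale for the hypothesis: odds ratios for ordered levels, against a percentage increase in SF12.

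**Working it through.** **Inputs.** From the article: 37 per workplace and 2 x 37 = 74 in total, which matches the stated total; SF12 measured before and after; three example job types. Not in the article: baseline SF12 mean and SD, within-person correlation r, number of SF12 levels, and which wave or waves enter the regression. Values for these below are assumptions.

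**1. What the job-type coefficient estimates.** Let job type j have expected health m + g_j before the policy and m + g_j + t + d_j after it. Here g_j is the standing gap from the reference job type, t is the change in the reference type, and d_j is the extra change in type j. With no period term and no baseline SF12:

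| Data entering the model | Job-type coefficient |
|---|---|
| Pre wave only | g_j |
| Post wave only | g_j + d_j |
| Both waves, equal numbers | g_j + d_j/2 |

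These are exact for a linear model and for a single wave on the logit's latent scale; the pooled row is approximate for a logit. If d_j = 0, every row gives g_j, which is pure baseline gap. The overall change t appears in no row. A time x job type term gives (g_j + d_j) - g_j = d_j, the quantity of interest.

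**2. Illustration.** One simulated data set was used (74 people measured twice, assumed true shift of 5 points, outcome cut into four levels). The ordered logit on a socio-economic covariate alone returned that covariate's coefficient, 0.58 (SE 0.17), and nothing about the policy. Adding a period term gave a pre/post log-odds of 1.08 (SE 0.31, not adjusted for clustering within person). A paired means test on the same data gave a change of 4.0 (t = 4.12, p = 0.0001). The change is therefore recoverable from the planned data, but not from the regression as described.

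**3. Scale of the hypothesis.** Read as a change in mean score, the hypothesis is a change of at least 0.25 x the pre-policy mean. For an assumed mean of 40 to 50 that is 0.25 x 40 = 10 to 0.25 x 50 = 12.5 points. An odds ratio does not convert to this. Nor does a test of zero difference at 0.05 test a minimum of 25%; for that, the confidence interval must be set against the 25% value.

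**4. Why pairing should be stated.** Take an assumed change of 0.33 SD, n = 74 and r = 0.3 to 0.7. The paired standardised change is 0.33/sqrt(2(1 - r)), and paired power is 66% to 95%. A test that ignored pairing would need a difference above 1.96 x sqrt(2/74) = 0.322 SD. Its power would be 52% to 53%, and its true type I error 2(1 - Phi(1.96/sqrt(1 - r))) = 0.019 down to 0.0003.

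**5. Two figures that are conditional only.**
- If both waves were stacked as independent rows, standard errors of person-level predictors would be too small by sqrt(1 + r): 1.22 for r = 0.5 and 1.30 for r = 0.7. A nominal 5% test would run at 2(1 - Phi(1.96/sqrt(1 + r))) = 11% to 13%.
- If a separate model were fitted in each workplace, the effective size with k equal levels would be 37(1 - 1/k^2) = 32.9, 34.7 and 35.5 for k = 3, 4 and 5. That supports about 2 to 3 parameters at 10 to 15 per parameter.

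**6. Can 74 people carry the replacement model?** The terms that describe change are time (1), time x workplace (1), time x job type (2 for three types) and time x sex (1), which makes 5, and 74/5 = 14.8 people per term. Adding one gender score makes 6, and 74/6 = 12.3. Both lie within the same 10 to 15 rule of thumb.

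**The case against.** The strongest defence is that the regression was never given the task of measuring the policy's effect. The same paragraph assigns the pre/post comparison to the means test, states the regression's purpose as association and job-type comparison, and nowhere calls it the main analysis. This stands. A reader might infer that Study A cannot estimate or test change at all; the article does not support that.

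A second defence is that a journal article condenses the full plan, and that pairing and repeated-measures terms are normally left to it. This stands for pairing and for any participant effect, on which the article is merely silent. It does not cover the predictors: the article names the socio-economic variables as the independent variables, and neither period nor baseline SF12 is a socio-economic variable.

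A third defence is that the alarming figures describe misuse that nobody has planned. This also stands. The article does not say that waves will be stacked, so the 11% to 13% error rate cannot be charged to it. The wording about each workplace does not commit to separate models of 37, and recruitment beyond the target is planned, so the limit of 2 to 3 parameters is conditional too.

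None of this answers step 1 of the working. Comparing job types on health level, in a study of change, mixes the standing gap with any differential change whichever wave is used.

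**Conclusion.** The point holds in a limited form. Study A names a test of overall pre/post change, but its only regression does not address change. Its job-type coefficients carry the baseline gap: in full if one wave is used, and with only about half of any differential change added if both waves are pooled. The size cannot be given in SF12 points because the article reports no baseline values by job type. The conclusion rests on the stated outcome and predictors alone and needs no assumption about correlation or stacking.

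The mismatch between odds ratios and a 25% increase also holds, and no named analysis is tied to the 25% threshold. The failure to say that the means test is paired is a point to clarify, not an error. The matter is worth correcting before analysis because the regression's results are meant to guide later work.

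**What to change.** Replace or supplement the ordered logit with one repeated-measures model of the SF12 score in all participants:

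- fixed effects for time (pre/post), workplace and time x workplace;
- a short, pre-chosen set of time x characteristic terms (job type, and sex/gender) with their main effects;
- a random intercept for participant.

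If a job type exists in only one workplace, define its term within that workplace so that it stays estimable. Report the mean within-person change with its 95% CI. State what the 25% is a percentage of (for example, the pre-policy mean) and read the interval against that value. State that the pre/post means test is paired. Keep ordinal models, with the same terms, for genuinely ordinal items.

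For comparisons between groups only, post SF12 adjusted for baseline SF12 is an acceptable alternative. It is not a substitute for the main estimate: with no untreated group it has no time term and does not itself estimate the overall pre/post change.

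The cost is a few lines of wording and slightly more analysis work. SF12 is already collected at both stages, so no new data are needed, and the planned software, SPSS, fits these models.
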